### Safety analyses

The population for safety analyses will include all participants enrolled in the trial. Participants will be informed the potential adverse events related to acupuncture procedure such as bruises, hematomas, infection, pain, chondritis, during the signing of inform consent. Adverse events will be coded using the *World Health Organization (WHO) Adverse Reaction Terminology Dictionary*. The research assistant will follow-up the participant’s adverse event until it has resolved, subsided, stabilized, or the event is otherwise explained. Special attention will be given to those participants who have discontinued treatment due to adverse events or who experience serious adverse events.

### Health economic evaluation

The cost-effectiveness analysis will be performed using incremental cost-effectiveness ratio of acupuncture vs sham acupuncture, i.e., (cost of acupuncture minus cost of sham acupuncture)/(effectiveness of acupuncture minus effectiveness of sham acupuncture) as a health economic outcome.

The perspective of health service provider will be adopted when evaluating the costs of implementation of acupuncture as an adjunct treatment in the postoperative pain management in public inpatient setting. Only direct medical costs for two groups will be calculated. The costs to be included are staff time costs and treatment cost for patients. To estimate the staff time cost for making referrals, the time spent on each participant by each staff member will be recorded. The average number of minutes spent will be multiplied by the relevant salary rate per minute. The length of hospital stay will be recorded to estimate the cost by the multiplication of the number of inpatient days with inpatient hospital stay cost per day according to the most updated Government Gazette.

The acupuncture treatment cost will be estimated for each treatment in terms of acupuncturist’s time spent on delivering the treatment, including traveling time, multiplied by salary rate per minute. The cost of analgesics, acupuncture needles and other consumable will be calculated. The capital cost included the electric stimulator with 10% annual maintenance fee.

The effectiveness of acupuncture and sham acupuncture groups will be measured by quality-adjusted life expectancy using the AUC method which aggregates the PBMH value, measured by either SF-6D or EQ-5D-5 L, from baseline day to the study end day.

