We hypothesized that acupuncture, as an adjunct treatment, is effective and safe to reduce postoperative pain during the first 5 days following abdominal surgery for gynecological diseases as compared to a sham control. The overall objective of this study is to examine the safety and efficacy of a combined acupuncture treatment of electroacupuncture (EA) and intradermal auricular acupuncture (AA) as an adjunct treatment in reducing postoperative pain in patients after abdominal surgery for gynecological diseases, compared with sham EA in combination with sham AA. Specifically, to test the hypothesis, the objectives of the study are:To determine the efficacy of acupuncture as an adjunct treatment in reducing postoperative pain as measured by the pain Numerical Rating Scale (NRS, the primary outcome) and pain medication consumption during the first 5 days after operation to be calculated as the area under the curve (AUC) to compare the between-group differenceTo determine whether the acupuncture treatment can shorten the time to recovery as measured by time to recovery variables including time to recovery of postoperative bowel functions and food intake; time to ambulation and time to dischargeTo evaluate the safety of acupuncture treatment in postoperative pain in a hospital ward by comparing the number of subjects with adverse events, number of patients withdrawn and reasons of withdrawal in treatment group with the sham control groupTo assess whether acupuncture is cost-effective in improving the postoperative quality of life of patients using the Quality of Recovery-9 (QoR-9), Short Form-6 dimension (SF-6D), and EQ-5D-5 L when compared with sham acupuncture

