### Participants

#### Sample size estimation

Results from an earlier study of EA as an adjunct treatment in postoperative pain were used for sample size consideration [10], and the expected mean difference and standard deviations of AUC in 5 days for the treatment group and control group were obtained by simulation using R [21].

The mean difference of AUC between treatment group and sham group in the previous study [10] is 3.4 with standard deviations of 2.9 for the treatment group and 3.6 for the sham group (effect size = 1.04). A lower limit of the 70% confidence interval of the effect size which is 0.75 is applied [22]. A sample size of 30 per group can provide 80% power to reject the null hypothesis with a significance level of 0.05 using a two-sided, two-sample, unequal-variance *t* test. With an expected dropout rate of 15%, the final sample size is 72 (36 per group). AUC is used to calculate the primary outcome measure because it provides information regarding the pain relief across the whole period, which is more meaningful than comparing the pain score at a particular time point. AUC also has an advantage in that it avoids multiple comparisons and thus will not inflate type I error. This statistical analysis approach has been widely used and reported by previous studies, including those published in leading pain journals [23, 24].

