### Measures

#### Outcome assessment

Subjects will be closely monitored during and after the operation. The primary outcome will be participants’ postoperative pain scores at rest measured by Numerical Rating Scale (NRS) for the first 5 days after operation. The secondary outcomes include postoperative NRS pain scores while coughing; dose and frequency of rescue analgesic use during hospital stay; time to recovery variables; QoR-9, SF-6D, and EQ-5D-5 L. If at any time point after the operation, a participant is unable to be managed according to the protocol for any reason, such as the development of complications, no further data will be collected. Telephone follow-up will be offered for participants discharged before day 5 (Fig. 2).

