Fourthly, it is not appropriate to regard sham acupuncture as a mere placebo or control group, although non-insertion sham acupuncture has been chosen in this study to maximize the treatment between the two groups [48]. Treatment costs incurred in the sham acupuncture arm involve sham acupuncture needles which will be assumed to cost the same as the acupuncture needles. The treatment efficacy of the sham acupuncture will not be assumed to be the same as that for the control group. In line with a previous randomized, sham-controlled trial alongside cost-effectiveness analysis of acupressure [49], the sham arm was one of the study arms for effectiveness and cost-effectiveness evaluation. Therefore, sham acupuncture will be considered as one competing intervention in the cost-effectiveness analysis.

Though there are many difficulties, the quality of the trial will be closely monitored by the Data and Safety Monitoring Board (DSMB) which is an independent board composed of a biostatistician, a senior Chinese medicine practitioner, and an anesthesiologist. It is hoped that this study will provide high-quality evidence on the efficacy and safety of acupuncture for alleviating postoperative pain as well as useful information for health economic analysis.

We hope that our findings will advance knowledge on the effectiveness of acupuncture in routine integrative medicine practice in Hong Kong hospital settings.

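### The only decision statistic named for the cost-effectiveness objective is a ratio whose denominator the trial was not sized to detect; incremental net benefit would be safer

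*Protocol article*

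**What the plan says.** The fourth objective in the Background is to "assess whether acupuncture is cost-effective in improving the postoperative quality of life of patients". The section Health economic evaluation then fixes the statistic: "The cost-effectiveness analysis will be performed using incremental cost-effectiveness ratio of acupuncture vs sham acupuncture". It writes the ratio out as cost difference over effect difference and calls it a health economic outcome. The abstract also names the ratio.

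The denominator is a utility area under the curve, "measured by either SF-6D or EQ-5D-5 L, from baseline day to the study end day". The article does not define the study end day. Treatment and the primary pain outcome cover five postoperative days, and "Telephone follow-up will be offered for participants discharged before day 5".

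On the cost side, sham treatment follows the same schedule and duration as acupuncture (Sham acupuncture group, Procedure). Its costs "involve sham acupuncture needles which will be assumed to cost the same as the acupuncture needles" (Discussion), and "sham acupuncture will be considered as one competing intervention in the cost-effectiveness analysis". Staff time for making referrals is recorded for each participant, after which "The average number of minutes spent will be multiplied by the relevant salary rate per minute".

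The sample size of 72 rests on pain AUC only. Statistical analyses says that secondary outcomes were not part of the power calculation and should be considered exploratory.

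**The concern.** A ratio supports a decision only when its denominator is clearly different from zero. If the denominator can plausibly be zero, the confidence set for the ratio is unbounded.

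The sign of the ratio alone does not give the decision either. A negative value arises when acupuncture is better and cheaper, and also when it is worse and dearer. A positive value arises when it is better and dearer, and also when it is worse and cheaper, where the decision rule reverses.

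Both parts of this ratio may lie near zero. The trial was not sized for utility, and the two arms share schedule and needle cost, so the cost difference rests largely on length of stay and analgesics. What is at stake is whether the named statistic can answer the cost-effectiveness objective. The primary outcome is not affected.

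**Working it through.** **The plan's own sample size.** Effect size = 3.4 / √((2.9² + 3.6²)/2) = 3.4 / 3.269 = 1.04, as stated. At the design value of 0.75, 30 per arm gives 81.5% power (two-sided 0.05, t test). 30 / 0.85 = 35.3, so 36 per arm and 72 in total. The figure reproduces, but it concerns pain AUC. The article gives no size for the utility difference.

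**When the interval for the ratio is finite.** A 95% Fieller interval is bounded only if the denominator itself differs from zero at two-sided 0.05. The probability of a finite interval is therefore the two-sample t-test power for the standardised utility difference d:

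| d | 30 per arm | 36 per arm |
|---|---|---|
| 0.2 | 12% | 13% |
| 0.3 | 21% | 24% |
| 0.4 | 33% | 39% |
| 0.5 | 48% | 55% |
| 0.6 | 63% | 71% |
| 0.75 | 81% | 88% |

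The probability reaches 50% at d = 0.51 (30 per arm) and d = 0.47 (36 per arm).

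**An illustration on the utility scale.** Assumptions, none from the article: true gain in mean utility 0.05, SD of a patient's mean utility 0.2, range 0.1 to 0.3. With 36 per arm and the normal approximation:

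- SE = 0.2 × √(2/36) = 0.047, so z = 0.05 / 0.047 = 1.06.
- P(wrong-signed denominator) = Φ(−1.06) = 14%. It is 2% at SD 0.1 (z = 2.12) and 24% at SD 0.3 (z = 0.71).
- P(unbounded) = Φ(1.96 − 1.06) − Φ(−1.96 − 1.06) = 81%. It is 44% at SD 0.1 and 89% at SD 0.3.
- At SD 0.2, a finite interval in half of repeats needs a gain of about 1.96 × 0.047 = 0.09.

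With 30 per arm the wrong-sign probability is 17% (3% to 26%) and the unbounded probability 84% (51% to 90%).

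**A larger gain.** With a gain of 0.10 and 36 per arm, the interval is finite in 55% of repeats at SD 0.20 and in 80% at SD 0.15.

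**Length of the window.** A gain of 0.05 over an assumed five days is 0.05 × 5/365 = 0.0007 QALY. The factor 5/365 multiplies both the difference and its SE, so it cancels from z and from every probability above.

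**Sign of the ratio, one scenario.** Take gain 0.05, SD 0.2, 36 per arm, a true cost difference of zero, and independent cost and effect estimates. Acupuncture is then better and cheaper in 86% / 2 = 43% of repeats, and better and dearer in 43%. It is worse and dearer in 14% / 2 = 7%, and worse and cheaper in 7%. A negative ratio, seen in about half of repeats, would mean dominated in about one case in seven.

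**The alternative.** Incremental net monetary benefit is λ × (effect difference) − (cost difference), a difference of means for any willingness-to-pay value λ. Its interval is finite at every d, and its sign has one meaning.

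**The case against.** The strongest reply is that the ICER is the standard summary measure and that the article only condenses the plan. It does not say that a point ratio alone will be reported, or that an interval, bootstrap or acceptability curve will be left out. Such details may sit in a full protocol or analysis plan that is not shown. This reply stands in part: nothing here rests on their absence. The point concerns the statistic that the article does name for a yes/no objective.

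Four stronger readings are tempting, and the documents do not support them.

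- **That the ratio will usually lack a finite interval.** This needs d below about 0.5, and the article gives neither a utility difference nor an SD.
- **That the very small QALY difference is the cause.** It is small in absolute units, but the time scale cancels. What matters is the utility difference relative to its variability at 30 to 36 per arm.
- **That the sign must remain ambiguous.** The formula needs both differences, so the quadrant can be read from them if they are reported.
- **That averaging minutes prevents a patient-level analysis.** The averaging applies to referral time only. Length of stay is recorded, and acupuncturist time is costed for each treatment.

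Net benefit also adds no information. With z near 1 on the effect, its interval may be too wide to settle the objective.

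**Conclusion.** The point holds in a conditional form. The ICER is a poor sole decision statistic here, because its denominator may not differ clearly from zero in a trial sized on pain.

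Its size depends on a quantity that the article does not give. An unbounded interval is the more likely result if d is below about 0.47 to 0.51. If utility responded as strongly as pain is assumed to, the ratio would mostly be well behaved. The figures for a gain of 0.05 illustrate the lower end and are not a forecast.

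The change is worth making because it affects a stated objective and uses the same data. It bears on a secondary, unpowered part of the trial.

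**What to change.** In Health economic evaluation:

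1. Make incremental net monetary benefit the decision statistic, over a stated range of willingness-to-pay values. Give a 95% confidence interval from one bootstrap that resamples patients with their costs and QALYs together.
2. Keep the ICER as a descriptive figure, reported with the cost difference, the effect difference and the quadrant.
3. Label the cost-effectiveness analysis exploratory, in line with Statistical analyses.
4. Optionally, cost each participant's own recorded referral minutes in place of the average. This is a minor point.

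The cost is analysis wording only, with the same data and the same sample size. A range of willingness-to-pay values has to be named.

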#### Short Form-6 dimension (SF-6D) and EuroQol -5 Dimension-5 Level (EQ-5D-5 L)

Quality of life will be assessed by using a Chinese-translated and validated Medical Outcomes SF-6D and EQ-5D-5 L. The SF-6D and EQ-5D-5 L are a preference-based measure of health (PBMH) for economic evaluation. The SF-6D is composed of six multi-level dimensions, namely, physical functioning, role participation, social functioning, bodily pain, mental health, and vitality, whereas the EQ-5D-5 L has five dimensions for health status description: mobility, self-care, usual activities, pain/discomfort, and anxiety/depression. The SF-6D and EQ-5D-5 L value set [41, 42] for the Chinese population will be used to derive utility scores.

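### The QALY difference in the ICER includes baseline utility with no adjustment stated, and no base-case utility instrument is named

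*Protocol article*

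**What the plan says.** The protocol article, under Health economic evaluation, defines the ICER as the cost difference divided by "effectiveness of acupuncture minus effectiveness of sham acupuncture". Effectiveness is quality-adjusted life expectancy, obtained "using the AUC method which aggregates the PBMH value, measured by either SF-6D or EQ-5D-5 L, from baseline day to the study end day".

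Two instruments are planned. The section on the utility measures says: "The SF-6D and EQ-5D-5 L are a preference-based measure of health (PBMH) for economic evaluation". It derives utility scores from both with Chinese value sets. The cost-effectiveness objective in the Background also lists both, "using the Quality of Recovery-9 (QoR-9), Short Form-6 dimension (SF-6D), and EQ-5D-5 L when compared with sham acupuncture". No section says which of the two gives the main ICER.

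The article does not say how the between-arm QALY difference will be estimated or whether any covariate enters. The Student's t test in Statistical analyses is assigned to the NRS AUC and, as one option, to morphine consumption. It is not assigned to QALYs.

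**The concern.** The utility AUC starts at the baseline day, before any treatment can act. A difference between arms at baseline therefore counts in part as effectiveness. It also tends to carry forward, because patients with higher utility at baseline tend to have higher utility later. Randomization makes this imbalance a matter of chance, but with 36 per arm it need not be small beside a QALY difference built up over a few days. If the denominator is simply the difference in mean AUC, the ICER carries noise that data already in hand could remove.

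The instrument is a separate matter. SF-6D and EQ-5D-5L are different measures with different value sets, so the same patients can yield two QALY differences and two ICERs. With no base case named, a reader cannot tell which one was meant to carry the conclusion.

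**Working it through.** **The plan's own figure.** The article gives no utility SD, QALY difference or ICER precision. The only figure carried forward is 36 per arm, and it reproduces.
- Effect size: 3.4/√((2.9² + 3.6²)/2) = 3.4/3.269 = 1.04, as stated.
- At the effect size of 0.75 that is applied, 30 per group gives 81% power with the unequal-variance t test, against the stated 80%.
- Dropout: 30/0.85 = 35.3, so 36 per group and 72 in total.

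**Assumptions, not in the article.**
- Horizon T = 5 days. The text does not date the study end day; telephone follow-up is described only up to day 5, and the Fig. 2 schedule is not shown.
- Utility SD 0.15 at every assessment (range 0.10 to 0.20).
- Correlation ρ = 0.5 between any two assessments (range 0 to 0.7).
- Two possible schedules: baseline and day 5 only, or daily.

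**Ceiling.** 5/365.25 = 0.0137 QALY.

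**Chance imbalance at baseline.** SE = SD × √(2/36) = 0.15 × 0.2357 = 0.0354. The 95% range is ±1.96 × 0.0354 = ±0.069.

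**Weight of baseline in the trapezoid (w₀).** With two assessments w₀ = 0.5. With daily assessments the weights are 0.1, 0.2, 0.2, 0.2, 0.2, 0.1, so w₀ = 0.1.

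**Effect of the imbalance on the QALY difference.** Direct share = imbalance × w₀ × T/365.25. With carry-over, w₀ becomes w₀ + ρ(1 − w₀), which at ρ = 0.5 is 0.75 or 0.55.

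**Benchmark.** A utility gain of 0.05 at every assessment after baseline is worth 0.05 × (1 − w₀) × T/365.25.

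| | Baseline and day 5 | Daily |
|---|---|---|
| Direct share of ±0.069 | ±0.00047 | ±0.000095 (about 0.0001) |
| With carry-over, ρ = 0.5 | ±0.00071 | ±0.00052 |
| Same, SD 0.10 to 0.20 | ±0.00047 to ±0.00095 | ±0.00035 to ±0.00070 |
| Value of a 0.05 gain | 0.00034 | 0.00062 |
| Carry-over figure ÷ gain (SD 0.15) | 2.1 | 0.85 |

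T appears in both the shift and the benchmark, so for given weights the ratio in the last row does not depend on the horizon.

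**What adjustment buys.** Let V be the variance of a patient's AUC in units of SD² × (T/365.25)². Then V = (1 − ρ)Σw² + ρ. Regression on baseline removes [w₀ + ρ(1 − w₀)]². The SE of the QALY difference is SD × √V × √(2/36) × T/365.25. The one degree of freedom spent on the covariate is ignored.
- Two assessments, ρ = 0.5: V = 0.75, and 0.75 − 0.75² = 0.1875 after adjustment. The SE falls from 0.00042 to 0.00021, or 50%.
- Daily, ρ = 0.5: Σw² = 0.18, so V = 0.59, and 0.59 − 0.55² = 0.2875 after adjustment. The SE falls from 0.00037 to 0.00026, or 30%.
- Over ρ = 0 to 0.7 the reduction is 29% to 61% with two assessments and 3% to 46% with daily ones.

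**The case against.** The strongest reply is that the article never says the QALY comparison will be unadjusted. It defines each patient's measure and leaves the estimator open. Covariates for incremental QALYs are commonly set in an analysis plan, which is not shown here. That stands: a reader might infer a commitment to a raw difference in means, but the text neither states nor excludes one. The recommended regression even keeps the AUC as defined. What remains is that the ICER rule, as written, contains no baseline term and would be better with one.

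A reader might also infer that a baseline difference enters the QALY difference in full, or that it biases the result. Neither is supported. The direct weight is 0.5 or 0.1 depending on a schedule in a figure that is not shown, and the rest depends on an unknown correlation. If utility is measured daily and pre-operative utility says little about post-operative utility, the gain from adjustment is only about 3%. Baseline assessment precedes randomization, so the imbalance adds variance, and bias conditional on the imbalance observed, but no systematic bias.

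On the instrument, it is tempting to read the wording as permission to choose after seeing the results. It is equally compatible with computing the AUC once with each instrument, which the objective and the section on the utility measures suggest. The narrower criticism stands: no base case is named.

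Finally, the article describes its secondary analyses as unpowered and exploratory, which limits the severity.

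**Conclusion.** The point holds as a minor, free improvement. Under the stated assumptions, chance baseline imbalance at its 95% limits moves the QALY difference by an amount of the same order as a sustained 0.05 utility gain: about twice that gain with two assessments, and about 85% of it with daily ones. Baseline adjustment would lower the standard error by 50% or 30% at a correlation of 0.5, and by anything from 3% to 61% over the schedules and correlations considered. These sizes rest on an assumed horizon, SD, correlation and schedule, none of which the article gives. The lack of a named base-case instrument is a matter of the text alone and needs no assumption. The primary pain analysis and the sample size of 72 are not affected.

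**What to change.** In Health economic evaluation, or in the analysis plan if one exists:
- State that incremental QALYs will be estimated by regressing each patient's utility AUC on treatment arm and baseline utility, and that the arm coefficient is the ICER denominator.
- Name one instrument (for example EQ-5D-5L) as base case and the other as a sensitivity analysis, before the data are unblinded.

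Reporting incremental net monetary benefit with a bootstrap interval beside the ICER would be sensible because the denominator may be near zero, but it is optional analysis-plan detail.

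The cost is a few lines of wording. The AUC from the baseline day already requires baseline utility, and both instruments are already planned, so no patients, visits or questionnaires are added.
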